This study was initiated to assess whether a period of 1 week of brace immobilisation within non- or minimally displaced DRFs is safe and will lead to an equal functional outcome, earlier return to work, higher patient satisfaction and reduction of health care costs compared to 3 weeks of cast immobilisation. The hypothesis of the study is that 1 week of brace immobilisation is non-inferior to 3 weeks of cast immobilisation.

This randomised controlled trial will provide level 1 evidence on the optimal period and way of immobilisation for non- or minimally displaced distal radius fractures in adult patients. Literature indicates that a shorter period of immobilisation and immobilisation by bracing is safe and might even be beneficial.

This study protocol is based on the ‘DR PIP II: Distal Radius Plaster Immobilization Period II’ study protocol (NL62861.029.17) where 4 weeks versus 6 weeks of cast immobilisation is analysed within displaced and reduced DRFs [21].

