### Sample size calculation

The primary outcome will be the PRWE score at 6-month follow-up, of which the minimal clinically important difference is 11.5 points. To be conservative, we use a non-inferiority limit of 10.0. The SD of the PRWE is 14.0 [35]. With a power (1 − *β*) of 90% and a type I error (*α*) of 5%, a sample size of 34 patients per treatment group was calculated.

To allow a 10% drop-out, 74 patients will be included, 37 patients per treatment arm. We expect that all patients can be included within 1–1.5 year.

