### Statistical analysis

Data from the demographic data collection and the outcome parameters will be cleaned blindly from the treatment data. Data are presented as mean scores with 95% confidence intervals. Linear regression analysis will be performed if data are not normally distributed.

A blinded evaluation of the trial patient’s functional status will be performed by a research assistant by use of the PRWE and qDASH scores. Blinded radiographic evaluation will be performed the intervention group and the control group. An independent expert will assess the degree of dislocation on an X-ray, blinded from the first assessment. Final blinded analysis of the primary outcome parameters will only be performed after 6-month follow-up.

The analysis of this study will be carried out according to the intention-to-treat principle, i.e. the patients will remain in the group they will be randomly allocated to at the baseline. Analysis of functional outcome will be assessed using repeated-measures analysis of variance (GLM 4) with the time as the within-group factor and the treatment as the between-group factor. The post hoc analysis will be performed on the time of randomisation. Group comparisons at different time points will only be made when the overall repeated-measures tests are statistically significant. All scores will be tested for normality using the Kolmogorov–Smirnov test. Parametric variables will be compared using the Student’s *t*-test, while non-parametric and ordinal variables will be compared using the Mann–Whitney *U* statistic. Nominal variables will be compared across independent groups using the chi-squared test or Fisher’s exact test. Homogeneity of variance will be assessed using Levene’s test.

Baseline characteristics that will be analyses are gender, age, dominancy, fracture side, fracture characteristics, smoking and osteoporosis. The outcome will be tested for normality and according to the outcome mean or median baseline characteristics will be compared.

Primary and secondary outcome measures are functional outcome (PRWE and qDASH), return to work, range of motion, pain, radiological outcome, complications and cost-effectiveness.

Missing data of the PRWE and qDASH score during follow-up can be imputed using multiple imputation based on baseline characteristics

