The PRWE questionnaire will measure the primary outcome (PRWE after 6-month follow-up). In this questionnaire, pain and function are scored on a 0 to 10 scale. The total score can range between 0 and 100, with 0 being the best possible outcome and 100 the worst. The outcome will be tested for normality, and according to the outcome mean or median PRWE after 6 months will be calculated. The mean or median outcome after 6 months in the intervention group (e.g. 1 week of brace immobilisation) will be compared with the control group (e.g. 3 weeks of cast immobilisation). A *t*-test will be used to compare the different outcomes. A *p* value of < 0.05 will be taken as a threshold of statistical significance. To check for clinically relevant results, we will compare the outcomes between the two groups to check whether this difference will reach the minimal clinically important difference of the PRWE of 11.5. Different variables will be compared between the two treatment groups (e.g. 1 week of brace and 3 weeks of cast immobilisation groups). In addition, if possible, a multivariate analysis will be performed, to compare different secondary outcomes to the period of brace or cast immobilisation. Depending on the amount of missing data, we will impute outcomes using multiple imputation based on age, sex, smoking and fracture characteristics. For all analysis, SPSS statistical software (version 28.0) will be used, in which two-tailed *p* value < 0.05 will be considered significant.

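### The stated imputation models leave out the randomised arm, so imputing would shrink a true PRWE difference by about the fraction missing

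*Protocol article*

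**What the plan says.** The Statistical analysis section of the protocol article describes imputation twice.

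- After the list of outcome measures: "Missing data of the PRWE and qDASH score during follow-up can be imputed using multiple imputation based on baseline characteristics". The same section lists those characteristics: "Baseline characteristics that will be analyses are gender, age, dominancy, fracture side, fracture characteristics, smoking and osteoporosis".
- In the paragraph on the primary outcome: "we will impute outcomes using multiple imputation based on age, sex, smoking and fracture characteristics". This is conditional: "Depending on the amount of missing data". No threshold is given.

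The two lists differ: hand dominance, fracture side and osteoporosis appear only in the first. Neither contains the treatment arm or the 6-week PRWE or qDASH. Both scores are collected at 6 weeks (Methods/design) and at the emergency department as baseline data (Sample and selection criteria).

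The analysis that the imputation feeds is a comparison of 6-month PRWE between arms. The Background gives its purpose: "The hypothesis of the study is that 1 week of brace immobilisation is non-inferior to 3 weeks of cast immobilisation". The Sample size calculation fixes the margin: "we use a non-inferiority limit of 10.0".

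**The concern.** An imputation model should contain the variables of the analysis that follows it, and here that means the arm. If the arm is absent, the model assumes that patients with missing scores have the same expected PRWE whichever treatment they received. The imputed part of the data then carries no treatment difference and dilutes the observed part.

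In a superiority trial such dilution would be conservative. In this trial the null hypothesis is that brace is worse by 10 points or more, and under that null, dilution moves the result towards the claim. Imputation is also most likely to be used when much is missing, which is when the dilution is greatest.

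**Working it through.** **Inputs from the protocol article.** Margin 10.0, SD 14.0, power 90%, alpha 5%, 34 per group before drop-out, 10% drop-out, 37 per group recruited (all from Sample size calculation). Imputation predictors as quoted above.

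**The plan's own figure.** n per group = 2 × (z₁₋α + z₁₋β)² × SD² / margin².

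- One-sided 5%: 2 × (1.645 + 1.282)² × 196 / 100 = 33.6, so 34. This matches; power at 34 is 90.3%.
- One-sided 2.5%: 41.2, so 42. This does not match.

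The sample size therefore rests on one-sided 5%, whereas the Statistical analysis section sets two-tailed 0.05, which corresponds to one-sided 2.5%. Both levels are shown below.

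**Shrinkage.** Let Δ be the true difference and f the fraction missing, equal in both arms and completely at random. Randomisation balances the baseline covariates, so imputed values have the same expected mean in both arms. Then

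E[estimate] = (1 − f) × Δ + f × 0 = (1 − f) × Δ.

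With Δ = 10 this gives 9, 8 and 7 for f = 10%, 20% and 30%.

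**Simulation at the margin.** 37 per arm, SD 14, true difference 10, 20 imputations, Rubin's rules with small-sample degrees of freedom, 4,000 runs. Non-inferiority is declared if the upper confidence limit is below 10. Assumptions not in the document: correlation of 0.6 between 6-week and 6-month PRWE, correlation of 0.2 with a baseline covariate, the same 10-point difference at 6 weeks, and missing fractions above 10%.

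| Imputation model | Missing | Mean estimate | Error, one-sided 5% | Error, one-sided 2.5% |
|---|---|---|---|---|
| As written | 10% | 8.94 | 7.0% | 3.2% |
| As written | 20% | 7.96 | 9.6% | 4.6% |
| As written | 30% | 6.98 | 12.7% | 5.8% |
| Arm added | 10% | 9.99 | 5.5% | 2.7% |
| Arm added | 20% | 10.04 | 4.8% | 2.2% |
| Arm added | 30% | 9.86 | 5.4% | 2.7% |
| Arm and 6-week score added | 10% | 10.04 | 5.0% | 2.6% |
| Arm and 6-week score added | 20% | 10.08 | 4.8% | 2.4% |
| Arm and 6-week score added | 30% | 9.93 | 4.8% | 2.1% |

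The Monte Carlo standard error is about 0.3 percentage points at 5% (√(0.05 × 0.95 / 4,000)) and about 0.25 at 2.5%. A second simulation (3,000 runs, 10 imputations, uninformative covariates) gave 6.6%, 8.6% and 11.6% at one-sided 5% for the model as written, and 2.9%, 3.7% and 5.5% at one-sided 2.5%. A third gave about 6%, 9.5% and 12.6% at one-sided 5%.

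**No true difference.** With Δ = 0 the model as written gives mean estimates of 0.08, 0.04 and 0.08, so there is no shrinkage.

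**What the 6-week score adds.**

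- *Drop-out at random.* The arm alone already removes the bias. The gain from the 6-week score is in precision: at Δ = 0 and one-sided 5%, power is 88.9%, 84.6% and 79.1% with the arm alone, and 88.6%, 86.8% and 83.0% with both (2,000 runs, Monte Carlo standard error about 0.8 points).
- *Drop-out that rises with a worse 6-week score.* The drop-out probability at an average 6-week score was set to 10% or 20%, which gives about 14% or 24% missing overall. The estimates are 8.24 and 6.91 as written (error 8.9% and 15.0%), 9.47 and 9.25 with the arm (6.3% and 7.0%), and 9.92 and 10.00 with both (5.1% and 4.6%).

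**The case against.** **The lists may not be exhaustive.** The article names what the imputation is based on and does not say that nothing else enters. It condenses a fuller protocol that is not shown. The first statement covers scores during follow-up, so the 6-week and 6-month scores might be imputed together and inform each other. In that case, even without the arm, the estimates would be 9.67, 9.32 and 8.90 at 10%, 20% and 30% missing, under the assumptions above. This stands as a limit on certainty. It does not remove the point: predictors are stated twice, the arm is in neither list, and an analyst following the text would leave it out.

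**A reader might infer that both omissions cause the shrinkage.** They do not. With data missing completely at random, adding the arm alone restores the estimate to about 10. The 6-week score matters for bias only if drop-out depends on 6-week status, and the document does not say whether it does.

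**A reader might infer that the trial is biased towards non-inferiority whatever the truth.** That is too strong. The bias favours the claim only if brace is truly worse. If brace is better, shrinkage works against it. The Background expects equal function.

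**The planned missingness is low and the imputation optional.** The document allows for 10% drop-out; 20% and 30% appear nowhere in it. At 10% the loss is about 1 point on a 0 to 100 scale. At one-sided 2.5% the second simulation's 2.9% cannot be told apart from the nominal level (Monte Carlo standard error about 0.3 points). If no imputation is done, no bias arises from this source. All of this stands and lowers the severity.

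**Rubin's standard errors are too wide here.** In the second simulation the mean reported standard errors were 3.52, 3.72 and 3.98, against empirical values of 3.09, 2.96 and 2.82. This partly offsets the bias, and the error rates above already include it.

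**Conclusion.** The point holds for the treatment arm. Followed as written, the imputation shrinks a true 6-month PRWE difference by about the fraction missing. This result is algebraic and needs only equal missingness at random in both arms. The error rates rest in addition on normal data with SD 14 and 37 per arm; the figures for the 6-week score also rest on the assumed correlations and the assumed 6-week difference.

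At the protocol's own 10% drop-out the consequence is modest, at about 1 point at the margin with a small rise in false non-inferiority. It becomes material only at missingness that the document does not plan for. A must-fix rating would be a stronger reading than the documents support, because the imputation is conditional, the planned missingness is low, and the direction favours the claim only when brace is worse. The severity is moderate. It still merits correction, because it touches the primary endpoint and errs towards the claim under the null hypothesis that the trial has to reject.

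**What to change.** In both places in the Statistical analysis section, use one consistent predictor list. State that the imputation model for PRWE and qDASH includes the treatment arm, or that imputation is done separately by arm. State that it also includes the baseline and 6-week PRWE and qDASH, in addition to the variables already listed. The arm removes the shrinkage; the 6-week scores recover precision and protect against bias if drop-out follows 6-week status. Age and sex, on which randomisation is stratified, are already in both lists.

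The cost is a sentence in each place. All of these variables are already collected, and neither the sample size nor the visit schedule changes. The change should be made before the analysis.

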### Ethical approval

This study had been approved by the Amsterdam UMC Ethical Board. Written, informed consent to participate will be obtained from all participants.

### Clinical trial registration

The study protocol of this study has been published on toetsingonline.com, trial registration of the Dutch Central Committee on Research Involving Human Subjects that meets the requirements of the ICMJE: https://www.toetsingonline.nl/to/ccmo_search.nsf/fABRpop?readform&unids=CEE3EDCF24F7B5B4C1258A64000B484F.

## Discussion

Three weeks immobilisation for non- or minimally displaced DRF is proven to be safe and sufficient [12].

In this study, adults < 50 years of age with a non- or minimally displaced DRF will be randomised between 3 weeks of cast immobilisation and immobilisation by a brace for 1 week. This option of treatment has been described in literature and guidelines, but is not generally used [18, 20, 34].

The incidence of volar plating as treatment of DRFs has been increasing, especially in displaced DRFs [36]. Non- or minimally displaced DRFs do not need reduction and operative fixation and have been treated by cast immobilisation since history [37].

Literature shows that wrist joint stiffness is correlated with a longer period of immobilisation [5, 6]. Wrist stiffness may lead to a restricted range of motion and worse functional outcome. It is believed that stiffness is caused by restricted movement during cast immobilisation over a longer period of time [5]. The ideal treatment of DRF will be as short as possible, safe and will lead to an early return to work or daily activities, which is especially important in young and vital patients. Still, level I evidence on this subject is rare. Both the Cochrane Review and the AAOS do not provide a clear treatment advice on the optimal period of immobilisation and do not favour immobilisation by cast or by brace [32, 38].

Therefore, it is important to provide level I evidence on bracing of DRFs. This study is designed as a randomised controlled trial with a non-inferiority design. Also, cost-effectiveness will be taken into account. The shorter the period of immobilisation, the earlier independency and return to work or school can be achieved, which will improve cost-effectiveness as well. Primary outcome of this study is the PRWE score after 6-month follow-up. The sample size of this study is based on the MCID of the PRWE. Functional self-reported outcome is considered as most important outcome factor. X-rays will also be analysed; however, secondary dislocation is not expected, as the non-displaced DRFs included in this study are considered to be stable. Furthermore, the correlation between radiological outcome and patient-reported outcome has been disputed in literature before. Functional outcome, especially patient-reported outcome, is the most important outcome factor. Radiological outcome does not always correlate to functional outcome, especially when aberrant outcome is subtle. But as very poor radiological outcome might influence other outcome factors, we chose to analyse this factor as well as a secondary outcome [39, 40].

This study will provide evidence on the optimal period of immobilisation in non-operatively treated displaced and reduced distal radius fractures. Both treatment options are accepted treatment protocols and both treatment options have a low risk of complications. Follow-up will be according to the current treatment protocol. This study will provide level 1 evidence on the optimal period and way of immobilisation for non- or minimally displaced distal radius fractures in adult patients.

## Trial status

Protocol number: 5, October 2023.

Date start of recruitment: approx. December 2024.

Approximate date recruitment to be completed: approx. December 2025.

## Data Availability

Data available upon request.

## Abbreviations

DRF: Distal radius fracture
qDASH: Quick Disabilities of the Arm, Shoulder and Hand score
PRWE: Patient-Related Wrist Evaluation
VAS: Visual analogue scale
ED: Emergency department
EQ-5D: EuroQol Group
iMCQ: I Medical Consumption Questionnaire
iPCQ: I Productivity Cost Questionnaire
AAOS: American Association of Orthopedic Surgeons
FU: Follow-up
X-ray: Radiography
GLM: Generalised linear regression
MCID: Minimum clinically important difference
